**Tertiary**
Diet (achievement of heart foundation target) [9]
Quality of life (SF12) [33]
Depression (Depression scale-short form) [34]
Angina status (Canadian Cardiovascular Society class) [35]
Modifiable risk factor knowledge (questionnaire) [19]
Cardioprotective medication use (hospital records and self-report)
Diabetic control (HbA1C)

Self-reported physical activity will be validated in a one-fifth subset of the cohort at 12 months by using accelerometers. Accelerometry is now considered the preferred method of objectively measuring physical activity as it provides data that allows individual examination of ambulatory activity frequency, intensity and duration [23,24]. For this trial an Actigraph GT1M (formerly Computer Science and Applications monitor), the most widely accepted accelerometer in research, will be utilised [25]. The matchbox size accelerometer will be attached to a belt that the participants in both the intervention and control groups will be asked to wear for a period of seven consecutive days at one year and three years. The Active Australia survey [26] records information from the seven-day period immediately prior to the survey, and therefore will be completed at the end of the week in which the accelerometer is worn. Thus the accelerometry data and Active Australia will record the same seven-day period.

To evaluate the generalisability of the previously proven CHOICE study [21], process measures of the intervention will include: record of participant recruitment, withdrawal from the program, the context of the interventions and the resources used. Barriers to implementation will be documented. Each participant will also answer questionnaires, which will determine the dose and exposure to the elements of the program. Through this we will examine fidelity of the program to the intervention components.

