### Sample size

Given the compelling evidence that lowering TC lowers cardiovascular events, our sample size is calculated based on change in TC. In the previous study with 70/group, we found a 25.5 (SD 1.0) mg/dL (0.66 mmol/L) greater reduction in TC at 12 months in the CHOICE than control group. To demonstrate a difference between CHOICE and CHOICE-*plus *groups, 138 per group in the RCT will give 80% power (2-tailed, P < 0.05) to detect a 0.35 SD effect (13.5 mg/dl (0.35 mmol/L) difference) in TC at 12 months or 3 years. To demonstrate a difference between the control and intervention groups at the single randomized site, 64 patients will be needed in the control group for 80% power. To allow for 20% loss to follow-up and a design effect of up to 1.15 (ICC 0.05) due to cluster sampling, a total of 400 patients will be recruited across the four sites.

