### Statistical analysis

Primary analyses will be conducted by intention-to-treat using SPSS for Windows (Version 12.01) and will be presented as mean and standard error of the mean or proportions. Differences in outcome measures, between and within groups, will be compared using repeated measures ANOVAs for continuous variables and either χ^2 ^tests or Fishers exact tests, as appropriate, for proportions of categorical variables. Two tailed p values of < 0.05 will be considered significant. Number needed to treat will also be calculated to estimate the number of patients who need to receive the CHOICE intervention to lower each of the major risk factors (TC, LDL-cholesterol, BP, smoking cessation, physical activity and overweight) to below current national targets.

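### Angina class is an ordered outcome, but the only tests named for categorical outcomes do not use the ordering; the power cost is conditional, from near zero to about 23 points

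*Protocol article*

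**What the plan says.** Table 2 of the protocol article lists "Angina status (Canadian Cardiovascular Society class") among seven tertiary end points. It gives no number of classes, no grouping and no cut.

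The Statistical analysis section gives one general rule for differences in outcome measures, between and within groups. They "will be compared using repeated measures ANOVAs for continuous variables", and otherwise with "either χ^2 ^tests or Fishers exact tests, as appropriate, for proportions of categorical variables". No rank test, trend test or ordinal model is named. The significance rule is "Two tailed p values of < 0.05 will be considered significant".

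The Sample size section rests on total cholesterol alone. It gives no power, effect size or class distribution for angina.

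**The concern.** CCS class grades severity: each step up is worse than the one below. It is not continuous, so under the article's two-way rule it is treated as categorical. A chi-squared or Fisher test on the class table gives the same answer if the class labels are shuffled. It therefore spreads a consistent move towards milder angina over several degrees of freedom. It can also be significant for a pattern that is neither better nor worse, which is hard to report as benefit or harm.

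The Discussion expects the programme to make recurrent symptoms less likely, and angina status is the only direct measure of cardiac symptoms in Table 2. What is at stake is the sensitivity and readability of that one outcome.

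**Working it through.** **Inputs from the article.** Two-sided alpha 0.05 (Statistical analysis). Group size: "138 per group in the RCT will give 80% power (2-tailed, P < 0.05) to detect a 0.35 SD effect". Control group: "64 patients will be needed in the control group for 80% power".

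**Assumed, because the article gives none of them.** The number of classes (3, 4 or 5), the class distributions, and a treatment effect that is a common odds ratio across classes.

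**The plan's own figure.** n per group = 2 × (1.96 + 0.8416)² / 0.35² = 2 × 7.85 / 0.1225 ≈ 128.1, so 129 (130 with the t distribution). With 138 per group, power = Φ(0.35 × √(138/2) − 1.96) = Φ(0.947) ≈ 82.8%. The stated 138 is slightly conservative. It concerns cholesterol and does not bear on this point; it is used below only as a group size.

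**Step 1, analytic.** Let an ordered 1-df test have noncentrality λ. If an unordered table of k classes carries the same λ on k − 1 df, its power is P(χ²(k−1, λ) > the 95th percentile of χ²(k−1)). For 80% power on 1 df, λ = (1.96 + 0.8416)² = 7.85.

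| Ordered test, 1 df | 3 classes, 2 df | 4 classes, 3 df | 5 classes, 4 df |
|---|---|---|---|
| 50% | 40.1% | 34.5% | 30.8% |
| 80% | 70.9% | 64.5% | 59.5% |
| 90% | 83.5% | 78.4% | 74.0% |

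At 80% the losses are 80 − 70.9 = 9.1, 80 − 64.5 = 15.5 and 80 − 59.5 = 20.5 points.

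**Step 2, simulation of the full class table.** 138 v 138, 20,000 runs per setting, Pearson chi-squared against the tie-corrected Wilcoxon test, with two to four assumed distributions per row. The odds ratio was set so that Wilcoxon had roughly the power in the column heading. Entries are points of power lost by chi-squared.

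| Classes | Wilcoxon ≈30% | ≈50% | ≈80% | ≈95% |
|---|---|---|---|---|
| 3 | 6.2 to 6.9 | 9.7 to 10.0 | 8.9 to 9.1 | 4.7 |
| 4 | 10.0 to 10.5 | 14.9 to 15.9 | 16.0 to 16.5 | 7.7 to 7.8 |
| 5 | 12.5 to 14.4 | 19.4 to 21.0 | 20.5 to 22.8 | 11.9 to 13.2 |

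The range is 4.7 to 22.8, or about 5 to 23 points. For 64 v 138, five classes and odds ratio 2.0, the losses lie inside it: 52.4 − 37.2 = 15.2 points with 70% in the lowest class, and 72.6 − 51.4 = 21.2 points with even classes.

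**Step 3, if the class is cut at lowest versus the rest.** A 2×2 chi-squared test against Wilcoxon on the full scale, Wilcoxon near 80%, five classes:
- 80% in the lowest class: 80.2% v 80.2%, no loss.
- 70% in the lowest class: 79.9% v 80.8%, a loss of 0.9 points.
- Five even classes: 57.9% v 79.9%, a loss of 22.0 points.

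The place of the cut matters too. With classes at 70, 15, 10, 4 and 1% and odds ratio 1.8, cutting after the lowest class gives 54.7% against 55.5% for Wilcoxon. Cutting after the second class gives 34.1% against 55.3%.

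**Step 4, type I error.** With no effect, the chi-squared test rejected in 4.1% to 5.2% of runs.

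**Step 5, an effect that is not a one-way shift.** With one group at 70, 15, 10, 4 and 1% and the other at 70, 27, 2, 0.8 and 0.2%, chi-squared had 92.8% power, linear-by-linear 44.7% and Wilcoxon 9.9%.

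**The case against.** The strongest reply is that the article never assigns a test to angina. Its sentence on categorical variables is generic, and its reference to proportions fits a yes/no split. A chi-squared test for trend is itself a kind of chi-squared test and is not excluded. The outcome is tertiary and unpowered, and a condensed article commonly leaves the coding and test of such an outcome to a fuller document that is not shown here.

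Much of this stands as a limit on size. A reader might infer that the plan commits itself to an unordered test of all classes; it does not say so. A reader might also infer a fixed loss of 15 to 20 points. That suits four or five uncollapsed classes, a consistent shift and moderate power, and nothing in the article establishes those conditions. Nor does every cut lose materially, as Step 3 shows.

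A further fair point is that five-class tables with thin upper classes would often have expected counts below 5, so the article's own wording would point to Fisher's test rather than the Pearson test simulated here. Fisher's test ignores order as well, so the direction holds, but its exact loss was not computed.

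The reply does not remove the point. The rule is stated for outcome measures in general. The diet end point in Table 2 is worded as reaching a target, whereas angina is listed by class with no cut. The text as it stands leads an analyst to a test without order, or to a cut that could be chosen after seeing the data.

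**Conclusion.** The point holds in a limited form. CCS class is ordinal, and the article's rule for categorical outcomes names only tests that do not use the ordering. For the full class table and a one-directional shift, the cost is about 5 to 23 points of power, entirely conditional on the assumed classes, distribution and effect. For a lowest-versus-rest cut it can be close to zero when most patients are in the lowest class.

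This is a matter of efficiency and interpretation. Type I error is sound, and no power statement in the article is contradicted, so it would be wrong to read the point as a threat to the validity of the trial or to its primary outcomes. It is a desirable improvement to a tertiary outcome.

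**What to change.** Add one sentence to the Statistical analysis section, for example: *CCS angina class will be compared between groups with a proportional-odds model adjusted for baseline class; chi-squared and Fisher tests are kept for nominal and binary outcomes.* A Wilcoxon or linear-by-linear trend test would serve equally well as the named method. One of them should be chosen in advance, and the choice should not depend on how the model fits the trial data.

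The cost is a sentence of wording and standard software, with no extra patients or measurements. The downside is small: an ordered test is less sensitive to effects that do not run in one direction, as Step 5 illustrates.

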As described elsewhere, the CHOICE intervention includes a one-hour initial consultation and follow-up phone calls over three months [20]. The program is designed to have an individualised, structured, case-management approach and is overseen by treating physicians. The development and implementation of the CHOICE program can be divided into four stages (figure 2). Stage one involves the development of modules and tailoring of leaflets to access recommended local services [21]. Stage two is a face-to-face risk factor assessment, lasting approximately one hour in which the patient is assisted to generate a list of their own relevant risk factors. In stage three, patients make guided choices about which risk factors they will address, participate in realistic goal-setting informed by national targets (table 1) [9] and then select management option(s) for lowering risk. The relevant patient information leaflets, described in Stage 1, support these choices. All CHOICE patients participate in the core module for lowering cholesterol as well as up to two choice modules from blood pressure (BP)-lowering, smoking cessation, increased physical activity and nutrition. Patients will have the option to add additional modules on completion of the three-month program. Additional module information will be given over the telephone and written information will be mailed to the patient. Stage four, is telephone follow-up, consisting of approximately four calls of around 10 minutes duration over a three-month period, during which each patient's risk factor(s) goals and strategies are re-evaluated and mutually changed if necessary. CHOICE-*plus *patients will receive additional telephone follow-up over 3 years as previously outlined (figure 1).

**Table 1 T1:** Risk factor targets

**Risk factor**	**National Heart Foundation of Australia targets **[9]
Smoking	Complete cessation
Nutrition	Establish and maintain healthy eating
Alcohol	Low risk alcohol consumption
Physical activity	30 minutes of moderate activity on most days of the week
Healthy weight	Waist measurement
	Male ≤ 94 cm Female ≤ 80 cm
	BMI 18.5–24.9 kg/m^2^
Lipids	LDL < 2.0 mmol/l
	HDL > 1.0 mmol/l
	Triglycerides < 1.5 mmol/l
Blood pressure	Adults ≥ 65 (unless they have diabetes and/or renal insufficiency and/or proteinuria ≥ 0.25 g/day) <140/90 mmHg
	Adults <65 years; adults with diabetes and/or renal insufficiency and/or proteinuria 0.25–1.0 g/day <130/80 mmHg
	Adults with proteinuria >1 g/day <125/75 mmHg

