### Outcome measures

The primary outcomes are TC, systolic blood pressure (SBP), smoking rates and physical activity levels at 12 and 36 months (Table 2). Secondary outcomes include readmission rates, all-cause mortality, cardiac mortality, number of cardiac risk factors, waist circumference and process measures to assess barriers to implementation and fidelity to the intervention components (Table 2).

**Table 2 T2:** Trial end points

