**Primary**
TC (fasting blood sample)
SBP (resting digital reading) [27,28]
Smoking rates (self report confirmed with carbon monoxide meter) [29-31]
Physical activity (Active Australia Questionnaire validated by accelerometry) [24,26]

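### The planned test for the primary outcome smoking rates makes no use of baseline smoking status: it is valid, but gives up power that an adjusted or stratified all-patient analysis would recover at no cost

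*Protocol article*

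**What the plan says.** The Outcome measures section gives smoking equal primary rank: "The primary outcomes are TC, systolic blood pressure (SBP), smoking rates and physical activity levels at 12 and 36 months". Table 2 defines how it is measured, "Smoking rates (self report confirmed with carbon monoxide meter", but gives no denominator.

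The Statistical analysis section states "Primary analyses will be conducted by intention-to-treat", assigns continuous outcomes to repeated measures ANOVA and categorical ones to χ² "tests or Fishers exact tests, as appropriate, for proportions of categorical variables", and adds "Two tailed p values of < 0.05 will be considered significant". It also plans a number needed to treat for smoking cessation, among other risk factors.

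The Sample size section says "our sample size is calculated based on change in TC". No smoking prevalence, quit rate, relapse rate or power for smoking appears anywhere in the article.

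Two other points bear on this. In the Interventions section, cholesterol lowering is the core module for everyone, "as well as up to two choice modules from blood pressure (BP)-lowering, smoking cessation, increased physical activity and nutrition". And under Group allocation, baseline measurements are completed before randomisation.

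**The concern.** Smoking is not an entry criterion, so each arm mixes smokers and non-smokers. Patients who do not smoke at baseline cannot quit; they can only relapse or start. Most of what decides whether a patient smokes at 12 or 36 months is therefore known at baseline. A plain χ² test on all randomised patients treats that known part as random noise. The continuous outcomes get a repeated measures analysis, which is naturally read as including the baseline value. Smoking gets a test that cannot use it.

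At stake is a real effect being missed on one of four primary outcomes in a trial sized on another. There is also an ambiguity in the number needed to treat for cessation, which differs several-fold between all patients and baseline smokers.

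**Working it through.** **The plan's own figure.** The only power statement is for total cholesterol: "138 per group in the RCT will give 80% power (2-tailed, P < 0.05) to detect a 0.35 SD effect". The usual formula gives n = 2(1.960 + 0.842)² / 0.35² = 128.1, so 129 per group. At 138 per group, power is Φ(0.35·√(138/2) − 1.960) = 82.8%. The stated number is slightly conservative. The total follows from it: 2 × 138 × 1.15 / 0.8 = 397, against 400 stated. None of this concerns smoking; I take only 138 analysed per arm from it.

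**Inputs.**
- From the article: 138 per arm; two-sided 5%; χ² test; intention-to-treat.
- Inferred: smoking rates are taken over the whole arm, without adjustment.
- Assumed, because the article is silent: 20, 30 or 40% smokers at baseline; quit rates of 40% v 50%, 40% v 60% and 30% v 60%; relapse or uptake among baseline non-smokers of 0%, 3% in both arms, or 6% v 2%.

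**Where the loss comes from: one case by hand.** Take 30% smokers, 40% v 60% quitting and no relapse.
- Smoking at follow-up: 0.30 × 0.60 = 18% v 0.30 × 0.40 = 12%, a difference of 6 points.
- Unadjusted variance: (0.18 × 0.82 + 0.12 × 0.88)/138 = 0.2532/138, so the SE is 4.28 points.
- Variance within baseline smoking groups: (0.30 × 0.60 × 0.40 + 0.30 × 0.40 × 0.60)/138 = 0.144/138, so the SE is 3.23 points.
- The difference, 0.2532 − 0.144 = 0.1092, equals 0.30 × 0.70 × (0.60² + 0.40²). It is due to baseline smoking alone and makes up 43% of the unadjusted variance.
- Effect divided by SE: 6/4.28 = 1.40 unadjusted, 6/3.23 = 1.86 stratified.
- Unadjusted power by the two-proportion formula: null SE √(2 × 0.15 × 0.85/138) = 4.30 points, so Φ((6 − 1.96 × 4.30)/4.28) = 29%.

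**Simulation over the range.** There were 200,000 runs per row. Baseline smokers were drawn as Binomial(138, share) in each arm. The tests were Pearson χ² on whole arms, Pearson χ² among baseline smokers only, and Mantel-Haenszel on all patients stratified by baseline smoking. Each cell gives power in % at 20 / 30 / 40% baseline smokers.

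| Relapse | Quit rates | Unadjusted, all | Smokers only | Stratified, all | Gain, stratified over unadjusted (points) |
|---|---|---|---|---|---|
| 0% | 40 v 50% | 8 / 10 / 13 | 12 / 15 / 19 | 11 / 15 / 18 | 3.1 / 4.6 / 5.7 |
| 0% | 40 v 60% | 20 / 29 / 38 | 32 / 45 / 56 | 31 / 44 / 56 | 11.4 / 15.6 / 17.5 |
| 0% | 30 v 60% | 36 / 53 / 68 | 62 / 79 / 89 | 61 / 79 / 89 | 25.2 / 26.3 / 21.7 |
| 3% both | 40 v 50% | 8 / 10 / 12 | 12 / 15 / 18 | 9 / 13 / 16 | 1.6 / 3.0 / 4.1 |
| 3% both | 40 v 60% | 17 / 26 / 36 | 32 / 45 / 56 | 23 / 36 / 49 | 6.0 / 10.2 / 12.8 |
| 3% both | 30 v 60% | 31 / 49 / 65 | 62 / 79 / 89 | 45 / 68 / 83 | 14.2 / 19.7 / 18.5 |
| 6 v 2% | 40 v 50% | 24 / 23 / 24 | 12 / 15 / 19 | 33 / 33 / 33 | 9.2 / 9.8 / 9.4 |
| 6 v 2% | 40 v 60% | 43 / 48 / 55 | 32 / 45 / 56 | 56 / 63 / 70 | 13.6 / 15.1 / 15.2 |
| 6 v 2% | 30 v 60% | 60 / 71 / 80 | 62 / 79 / 89 | 78 / 88 / 93 | 18.2 / 17.3 / 13.5 |

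With no treatment effect (40% quitting in both arms, 0 or 3% relapse), the unadjusted and stratified tests both rejected in 4.9 to 5.1% of runs.

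**Number needed to treat.** With 30% smokers and a 20-point difference in quitting, it is 1/(0.30 × 0.20) = 16.7 over all patients and 1/0.20 = 5 among baseline smokers.

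**The case against.** **The method is inferred from one general sentence.** The article never says that whole arms are compared without adjustment, and an unseen analysis plan may fix the denominator. This stands in part. Whole-arm and unadjusted is the natural reading of a rate, intention-to-treat and a plain χ² test, but it remains a reading. The named tests do not themselves use baseline smoking, so the point concerns a stated method and not a missing detail.

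**Nothing is invalid.** This stands. A reader might infer that chance imbalance in baseline smokers biases the comparison. With 30% smokers, its SD is √(2 × 0.30 × 0.70/138) = 5.5 points. But randomisation makes it random, and the test's standard error already covers it. The cost is efficiency only.

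**The loss may be small.** Both arms get the same three-month program, and before the 12-month assessment the extra contact for CHOICE-plus is a telephone call at six months. Large differences in quitting have no support in the article. This stands: at 40% v 50% quitting the gain is only about 2 to 6 points. A reader might quote a loss of 12 to 27 points as a property of the plan. That range belongs to a smokers-only test with large quit differences and no relapse.

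**A smokers-only analysis could answer the wrong question.** Patients may enter up to eight weeks after the event, so recent quitters may be present, and reinforcement may work by preventing relapse. This also stands, against making smokers-only the primary analysis. At 6% v 2% relapse, 30% smokers and 40% v 60% quitting, its power is 45%, against 48% for the unadjusted test and 63% for the stratified one. Nor are the smokers-only and adjusted all-patient analyses equivalent once non-smokers relapse.

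**The number needed to treat may already be meant for smokers.** This is possible. The article does not say which denominator applies, so it cannot be called wrong, only open.

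**Conclusion.** The point holds as one of efficiency. The stated test is a valid intention-to-treat comparison, but it ignores a strong baseline predictor of a primary outcome. The stratified all-patient test had more power in every case tried, with its error rate near 5%.

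The size rests on assumed rates: about 2 to 6 points at 40% v 50% quitting, and about 6 to 26 points at 40% v 60% or 30% v 60%, with relapse of 0 to 3% equal in both arms. It is about 9 to 18 points if relapse is 6% v 2%. The documents do not support a claim of bias, of an inflated error rate, or of one fixed loss of power.

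Nor does the change rescue the outcome. Across these cases the stratified test has 9 to 93% power, and no more than 33% at 40% v 50% quitting.

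**What to change.** In the Statistical analysis section:

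1. Make the primary smoking analysis an intention-to-treat comparison of all randomised patients at 12 and 36 months, adjusted for or stratified by baseline smoking status (logistic regression or Mantel-Haenszel). Mantel-Haenszel copes better if few or no non-smokers relapse.
2. Define baseline smoking status from information obtained before randomisation, and say how patients who stopped at or after the index event are classed.
3. Report as supportive the carbon-monoxide-confirmed quit rate among baseline smokers and the unadjusted rate over whole arms.
4. Calculate the number needed to treat for smoking cessation among baseline smokers, and say so.

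The cost is a few sentences and one changed analysis of data the trial already collects, with no extra patients or procedures. The change should be made before outcomes are seen by arm. One small price is that the adjusted estimate needs more explanation than a raw difference; the supportive rates supply it.

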**Figure 1 F1:**
[figure not shown]
**Design of the CHOICE study**. ACS: acute coronary syndrome. CHOICE: Choice of Health Options In prevention of Cardiovascular Events.

Blinded assessments will be conducted at baseline and 36 months during a face-to-face interview. At 12 months, assessments will be completed by the intervention nurse and to ensure validity, a sample of 20 patients will have their measurements repeated by an independent assessor, blinded to group allocation. At follow-up assessments, additional data will be collected, including details of any unplanned hospital admissions, medications and doses and details of visits to the family physician, cardiologist and attendance at any community program pertaining to their heart health. Ethical approval for this study has been granted by Sydney South West Area Health Services and will be sought from the University of Sydney Human Research Ethics Committees. Written and informed consent will be obtained from all study participants prior to commencement.

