**Secondary**
Readmission rates (hospital records)
All-cause mortality (hospital records)
Cardiac mortality (hospital records)
Waist circumference (tape measurement) [32]
Number of modifiable risk factors (sum)
Process evaluation measures (including recruitment, withdrawal, barriers to participation, number and length of interventions delivered)

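### Neither analysis method stated for outcome measures suits "readmission rates", and the proportions test left for death depends on complete 36-month status

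*Protocol article*

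**What the plan says.** The Statistical analysis section has one sentence on group comparisons. It covers "Differences in outcome measures, between and within groups", which "will be compared using repeated measures ANOVAs for continuous variables", with chi-squared or "Fishers exact tests, as appropriate, for proportions of categorical variables" for the rest. It names no method for event times or for counts.

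The Outcome measures section lists the events as secondary: "Secondary outcomes include readmission rates, all-cause mortality, cardiac mortality, number of cardiac risk factors". Table 2 gives their source: "Readmission rates (hospital records" and "All-cause mortality (hospital records", both entries closing there. The text does not say whether a readmission rate is a proportion of patients, a count per patient or a count per unit of time.

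The Design section adds a second source for admissions. At follow-up assessments, "additional data will be collected, including details of any unplanned hospital admissions". Follow-up is three years for everyone.

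**The concern.** The analysis sentence is worded for outcome measures in general and offers two options. Death is a yes/no outcome, so only the proportions test fits it. Readmission can be pushed into either option, and each costs something.

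- **As yes/no.** A patient admitted five times counts the same as one admitted once, and an admission in month 1 the same as one in month 35. A patient who dies in month 2 without returning to hospital is scored as not readmitted, which is the favourable category.
- **As a count.** Repeated measures ANOVA assumes roughly normal errors and has no term for time at risk. Admission counts have many zeros and a long right tail, and patients who die or drop out have less time in which to be admitted.

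Readmission and mortality are the listed outcomes closest to the Discussion's expectation of fewer deaths, infarctions and recurrent symptoms, so a weak analysis here wastes information that the trial will hold anyway.

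**Working it through.** **No figure in the plan to reproduce.** The sample size is based on total cholesterol. The article gives no event rate, power or sample size for death or readmission, so the event rates, effects and overdispersion below are assumptions, shown as ranges. The alpha of 0.05, two-sided, is the article's. Arms of 200 are the total of 400 divided by two. This ignores the control patients, and smaller arms would lower power for both analyses.

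**1. Any readmission against counts, no loss to follow-up.** Let admissions per patient over three years be negative binomial with mean *m* in one arm and 0.7*m* in the other, and overdispersion *d*.

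- Probability of at least one admission: 1 − (1 + *d m*)^(−1/*d*).
- Proportions test: z = (p0 − p1) / √[p̄(1 − p̄) × 2/200].
- Count comparison: z = −ln(0.7) / √[(1/*m* + *d* + 1/(0.7*m*) + *d*) / 200].
- Power ≈ Φ(z − 1.96).

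Worked case, *m* = 1 and *d* = 1:

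- p0 = 1 − 1/2 = 0.500 and p1 = 1 − 1/1.7 = 0.412. The difference is 0.088 and its standard error 0.0498, so z = 1.77 and power is about 42%.
- Count variance = (1 + 1 + 1.429 + 1)/200 = 0.0221, standard error 0.149. Then z = 0.357/0.149 = 2.40 and power is about 67%.

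Simulation with 4,000 runs per row (counts compared by the log ratio of means with empirical variance):

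| Mean admissions | Overdispersion | Power, any readmission | Power, count |
|---|---|---|---|
| 0.5 | 0.5 | 43% | 54% |
| 0.5 | 1 | 37% | 49% |
| 0.5 | 2 | 25% | 39% |
| 1.0 | 0.5 | 54% | 78% |
| 1.0 | 1 | 43% | 68% |
| 1.0 | 2 | 29% | 53% |
| 1.5 | 0.5 | 56% | 87% |
| 1.5 | 1 | 41% | 76% |
| 1.5 | 2 | 28% | 57% |

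The formulas agree with the simulation to within about 2 points in every row. The count analysis is ahead throughout, and by more when admissions are frequent.

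**2. Proportions test against log-rank for a single event.** Exponential event times over three years, 200 per arm, 4,000 runs per scenario, control risk 5% to 50%, censoring independent of the event.

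- *Status known for all.* The proportions test has type I error of 4-5%.
- *20% of event status lost in both arms.* Type I error is 4-5% for every method. At hazard ratio 0.7, power for log-rank, for losses counted as event-free and for complete cases is 10/10/10% at 5% risk, 23/22/22% at 15%, 40/39/39% at 30% and 60/57/58% at 50%. Single-arm percentages do shift: a true 15% reads as 13.4% (event-free) or 16.5% (complete case).
- *30% lost in one arm and 10% in the other.* Type I error is 5-16% (event-free) or 6-10% (complete case), against about 5% for log-rank.

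Only the last case harms the comparison between arms, and its loss split is assumed.

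**The case against.** **A reader might infer that the plan mishandles the 20% loss it expects.** The documents do not support that. The allowance, "To allow for 20% loss to follow-up", belongs to a sample size for cholesterol, which needs a fasting blood sample and so attendance. Death and readmission come from hospital records, which do not need the patient to attend. With fixed follow-up and complete records, a proportions test on 36-month death is valid. Even if 20% of event status were lost equally in both arms, type I error would stay near 5% and power would be within about 3 points of log-rank. Distortion needs unequal or informative loss. The Interventions section makes unequal loss possible, since CHOICE-plus has contacts after three months that CHOICE does not, and admissions are also asked about at assessments. Nothing in the article says that it will occur.

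**A reader might also infer that the plan compares readmission as a proportion.** It does not say so. Readmission is not assigned to either method, and a per-patient count could be placed under the first. That does not rescue the plan, because repeated measures ANOVA is a poor method for such a count.

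**Other objections.** The analysis paragraph opens by referring to primary analyses, so its reach over secondary events is arguable. Methods for unpowered secondary outcomes are often left to an analysis plan, which is not shown. This limits the weight of the point. But the comparison sentence is worded for outcome measures generally and names specific methods, so there is a stated choice to improve. Log-rank and Cox analyses also assume non-informative censoring. They would not cure loss related to prognosis.

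**Conclusion.** The point holds in a limited form. Neither stated method suits readmission rates. If readmission is reduced to yes/no, power is 25-56% where a count analysis would have 39-87%, with no loss to follow-up. Those figures rest on 0.5 to 1.5 admissions per patient, a rate ratio of 0.7, overdispersion of 0.5 to 2 and 200 per arm, none of which the article gives for this outcome. The direction is the same across that range.

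For death, the proportions test is acceptable with complete 36-month status from records. It becomes vulnerable only if ascertainment is incomplete and differs by arm, a possibility that the article neither states nor rules out. No sample size or primary analysis changes.

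**What to change.** - Define readmission as the number of admissions per patient. Analyse it by negative binomial regression with an offset of log follow-up time (time alive and under observation) and site as a covariate.
- Analyse all-cause mortality by a log-rank test and Cox model stratified by site, censoring at last known status from hospital records.
- Keep chi-squared or Fisher tests for status measures such as smoking.

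The cost is a few lines of analysis text and recording the dates of admissions, deaths and last known status. Admission details are already to be collected at follow-up assessments.
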